### 8.1.3 Other study parameters

*Baseline data of study population necessary for Ava COVID-RED app algorithms (Collected at registration via the Ava COVID-RED app)*

- Date of birth
- Country of birth
- Biological sex
- Weight (kg)
- Height (cm)
- Previous COVID-19 testing history
- Risk-factors:
  - Hay fever
  - Moderate to severe asthma
  - Chronic smoker's cough
  - Chronic lung disease
  - Diabetes requiring medication
  - Hypertension requiring medication
  - Serious heart condition
  - Chronic kidney disease requiring dialysis
  - Chronic liver disease
  - Human immunodeficiency virus (HIV)

- Immune system deficiency or autoimmune disorder
  - Haemoglobin disorders (e.g., sickle cell disease, thalassaemia)
  - Chemo-, radio- or immunotherapy in the past 6 months
  - Use of medications that weaken the immune system (e.g., corticosteroids)
  - History of bone marrow or organ transplant
- Smoking status
- Vaccine history (past 12 months)
- Menstruation status including current Birth Control methods
- Breastfeeding status

*Baseline data of study population (Collected at registration and baseline in COVID-RED web portal)*

- Biological sex
- Country of birth
- Father country of birth
- Mother country of birth
- Age
- Height
- Weight
- Healthcare Professional (Y/N)

*COVID-19 Risk Factors (Collected at registration and baseline in COVID-RED web portal)*

- Risk factors
  - Hay fever
  - Moderate to severe asthma
  - Chronic smoker's cough
  - Chronic lung disease
  - Diabetes requiring medication
  - Hypertension requiring medication
  - Serious heart condition
  - Chronic kidney disease requiring dialysis
  - Chronic liver disease
  - Human immunodeficiency virus (HIV)
  - Immune system deficiency or autoimmune disorder
  - Haemoglobin disorders (e.g., sickle cell disease, thalassemia)

- Chemo-, radio- or immunotherapy in the past 6 months
  - Use of medications that weaken the immune system (e.g., corticosteroids)
  - History of bone marrow or organ transplant
- Highest educational level attained
- Household situation (e.g. total number of housemates)
- Employment details
- Use of public transport
- Use of CoronaMelder App (or similar application) and duration
- Previous SARS-CoV-2 infections
- Previous COVID-19 vaccine
- Chronic medication use

## 8.2 Randomisation, blinding and treatment allocation

This is a single-blinded study. The sponsor, Investigator and the device manufacturer will be aware of the assigned sequence, but the subject will be blinded. The randomization ratio for the study sequences will be 1:1. The randomization schedule will be stratified. Based on demographics, medical history and/or profession, each subject will be stratified at baseline into a high-risk and normal-risk group within each sequence. Within each study sequence, the normal-risk stratum will be capped in order to ensure that the high-risk stratum is fully recruited. The subject will wear the Ava bracelet and complete the Daily Symptom Diary in the Ava COVID-RED app for the full duration of the study, and they will not know if the feedback to them about their potential infection status will be only based on data they entered in the Daily Symptom Diary within the Ava COVID-RED app or based on both the data from the Daily Symptom Diary and the Ava bracelet.

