## 6. INVESTIGATIONAL PRODUCT

### 6.1 Name and description of investigational product(s)

Ava COVID-RED is an investigational product developed specifically for the COVID-RED clinical trial. The device uses machine learning and wearable sensor technology to help users monitor their general health and well-being. In particular, its algorithms are fine-tuned to detect changes in physiological and/or self-reported symptoms that could indicate a potential SARS-CoV-2 infection. Ava COVID-RED is a non-invasive device made up of the following components as illustrated in Figure 3 below:

- *The Ava Bracelet incorporating hardware with electronics and embedded software (Hardware Bracelet Generation 2.0)*
- *A mobile application running on smartphones (iOS and Android)*
- *Backend software, including the COVID-19 infection monitoring algorithm, running on remote servers.*

The wrist-worn bracelet acts as a data logger, recording and storing user's physiological sensor signals as raw datasets throughout the night. The user synchronizes the Ava bracelet to the mobile application (AVA COVID-RED app) the following morning. The mobile app reads out all the raw datasets via Bluetooth Low Energy (BLE) and transfers them to the backend. After computation and pre-processing of the physiological parameters based on the bracelet recordings, the COVID-19 infection monitoring algorithm is run. The obtained pre-processed physiological parameters and potential COVID-19 infection indications are transferred back to the mobile app and displayed to the user.

[figure not shown]

Figure 3: Ava-COVID- Visual of Components

The AVA COVID app is also utilized to collect the Daily Symptom Diary data. The user completes The Daily Symptom Diary in the app, and they will report any symptoms they may be experiencing. The app transfers this information to the backend server and the COVID-19 infection monitoring algorithm is run on the self-reported Daily Symptom Diary data only or in combination with the bracelet data depending on condition. Potential COVID-19 infection indications are transferred back to the mobile app and displayed to the user.

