#### **8.4.16 Interview with subject for Healthcare Resource Utilization (HRU) and Adverse device effect (ADE) reporting**

In the case of a hospital episode or ADE as reported by the subject, qualified medical health professionals will contact the subject directly by phone and obtain relevant information through a structured interview. Data on HRU and ADEs will be entered directly into the eCRF system. Additionally, the clinical team will report all ADEs and device deficiencies to the Ava bracelet manufacturers within 5 business days of notification from the subject. All potential or probably serious adverse device effects (SADEs) are to be reported by the clinical team to the device manufacturer within 24 hours of notification from the subject.

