#### 9.2.2 Serious adverse device effects (SADEs)

A serious adverse event, in general, is any untoward medical occurrence or effect that

- results in death;
- is life threatening (at the time of the event);
- requires hospitalisation or prolongation of existing inpatients' hospitalisation;
- results in persistent or significant disability or incapacity;
- is a congenital anomaly or birth defect; or
- any other important medical event that does not result in any of the outcomes listed above due to medical or surgical intervention but could have been based upon appropriate judgement by the investigator.

An elective hospital admission will not be considered a reason to consider an event serious. In this trial, we will restrict the recording of SAEs to only the device-related SAEs (SADEs). These will be reported to the manufacturer within 24 hours of receiving notification from the subject. Each SADE that may occur during the course of the COVID-RED clinical trial should be documented on the Spontaneous Adverse Event and Device Deficiency Report Form provided by the manufacturer, or on a similar form containing the same information as the form provided by the manufacturer. This form should also be completed for device deficiencies that could have resulted in a SADE under different circumstances. The Spontaneous Adverse Event and Device Deficiency Report Form must be completed in as much detail as possible, including at the minimum the device serial number and country of event. Whenever possible, pictures documenting the ADE, SADE and/or device deficiency should be included. The completed form should be sent to the following customer service support email address:

[[contact]](mailto:[contact])

Seriousness is judged by the study investigator (or delegate).

All serious adverse events that lead to (temporary) suspension/stop of the clinical trial or adjustment in the medical device and all unexpected serious adverse device reactions which indicate an imminent risk of death, serious injury, or serious illness and that require prompt remedial action for other patients/subjects, users or other persons, will be reported expedited to the CCMO and EC within 2 working days and not later than 4 calendar days.

All other serious adverse device effects will be reported quarterly to the CCMO and EC via the MEDDEV 2.7.3 form.

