### *Development and validation of algorithms*

As indicated in section 3.3, the algorithms applied in both the control and experimental condition will continually be developed during the trial with specific versions being released and evaluated throughout. During the Learning Phase and Period 1, first versions of the algorithms will be implemented which have been developed using data collected from previous studies and existing users of the Ava bracelet. Data collected during the Learning Phase will then be used to develop second versions of the algorithms which will be

implemented and statistically evaluated in Period 2. When all subject follow-up is complete and all data is collected, final versions of the algorithms will be developed. As such, the Learning Phase will primarily be used to collect both physiological and symptom data to train both algorithms, Period 1 to gain further understanding of the first version of the algorithm and enable blinded sequences, and Period 2 will be used to statistically evaluate the second version of the algorithm as specified in the primary objective.

For these analyses, the duration of implementation of different versions of the algorithms will be taken into account. As such, the performance of the implemented algorithms will be calculated using data collected during its implementation. In addition, the performance of different versions of the algorithms can be assessed by applying them retrospectively to all of the collected raw data. In this way, the algorithms will be judged as actually implemented in the trial (*de facto* estimation) and under a hypothetical condition wherein the final developed algorithm is treated as having been implemented for each subject (*de jure* estimation).

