## 10.7 Interim analysis

The applied algorithms in both study conditions will be updated using data gathered throughout the study and a new version will be implemented in Period 2 of the study. When evaluating the different versions of the algorithm as mentioned above, we will essentially obtain interim *de facto* estimates of the performance of these algorithms. The final version of the algorithm will also be retrospectively applied on the data of the subjects within the considered analysis sets to obtain a final *de jure* estimate of the performance. As this is not a traditional hypothesis testing study, there will not be any adjustments to the Type 1 error level (alpha) to account for any interim statistical analysis of trial data.

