Data from the eCRF and COVID-RED web portal will be pseudonymized (subjects will be assigned a unique identification number in Castor EDC) and stored in a study database (Castor EDC). Only authorised study staff (Sponsor/Investigator and Julius Clinical) will be allowed to enter data into the eCRF and make changes to eCRF data. In addition, only the Data manager and Physicians from UMCU carrying out the interviews will have access to subjects' personal data (Sponsor/Investigator and Julius Clinical) (APPENDIX 2).

The key to connect the identification number to the subject will be stored in a separate section of the EDC and will only be available for a limited number of study staff from the Sponsor/Investigator and Julius Clinical, such as the Data manager, Helpdesk of Julius Clinical, the Julius Clinical Data Transfer Lead and his/her delegate and Physicians at UMCU

carrying out the interviews in case of lost-to-follow up, hospitalization, or adverse device effect scenarios (APPENDIX 2).

Subject personal data (name and address) will also be shared with the vendor (Mailstreet) responsible for sending the onboarding and study supplies to the subjects. Since recruitment and follow-up will be completely remote, supplies will need to be sent to the subjects' home addresses (APPENDIX 2).

The Julius Clinical Data Transfer Lead and his/her delegate will request additional personal data (required for reporting to the GGD) in case the PCR sample taken by the subject themselves is positive. SARS-CoV-2 is a notifiable disease in the Netherlands and therefore all subjects who tested positive must be reported to the GGD, so that the GGD can initiate contact-tracing (see section 3.5 and 8.4.12).

Data points that originate from a third party database (e.g., Ava COVID-RED app, Ava bracelet and laboratory results from SARS-CoV-2 serology antibody testing), will be transferred via secure means to the investigator. Transferred data will not contain personal identifiers as only trial-specific identifiers will be used to link data between parties.

Data points that are not considered part of the eCRF (e.g., derived data points and administrative data points) will be automatically calculated or entered by authorised staff of Sponsor, Investigator or its designee.

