|----------------------------------------|-----------------------------------------------------------------------------------------|-------------------------------------------------------------------------------------------------------------------------|------------------------------------------------------------------------------------------------------------------------------------|-------------------------------------------------------------------------------------------------------------|
|                                        |                                                                                         | Yes, all personal identifiable information                                                                              | Data manager of JC, Helpdesk of JC (excluding test results)
JC Data Transfer Lead and his/her delegate (including test results) | username and password restrictions                                                                          |
| Mailstreet                             | Mailstreet                                                                              | Yes, information critical to send out study-materials (i.e. Name, Address)                                              | Mailstreet employees involved in COVID-RED study                                                                                   | ISO 27001 (information security) certified study                                                            |
| anDREa Analytics platform              | COVID-RED Consortium:
UMCU
AVA
Julius Clinical
Vive
UCL
Takeda | No,
Pseudonymized data from AVA (bracelet and symptom diary), Surveys, COVID-19 test results, Hospitalization events | Data scientists/researchers in the COVID-RED study team                                                                            | GDPR-compliant, Microsoft Azure AD accounts, audit-trails, pen-tested                                       |
| Julius Clinical AWS Analytics platform | COVID-RED Consortium:
UMCU
AVA
Julius Clinical
Vive
UCL
Takeda | No,
Pseudonymized data from AVA (bracelet and symptom diary), Surveys, COVID-19 test results, Hospitalization events | Data scientists/researchers in the COVID-RED study team                                                                            | AWS Servers, Restricted (account/password protected) access, MFA to platform, (audit) log trails, encrypted |

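### Staff who interview on healthcare use and decide on loss to follow-up belong to bodies that know the sequence, and the protocol gives two data sources and no freeze point for the V2 algorithms

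*Protocol*

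**What the plan says.** **Masking.** The trial is declared single-blinded throughout, and 8.2 spells this out: "The sponsor, Investigator and the device manufacturer will be aware of the assigned sequence, but the subject will be blinded". Section 6.1 describes where the assignment is used: on the back-end server the "algorithm is run on the self-reported Daily Symptom Diary data only or in combination with the bracelet data depending on condition".

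**Who collects and judges.** When a subject reports a hospital episode or device effect, 8.4.16 says "qualified medical health professionals will contact the subject directly by phone and obtain relevant information through a structured interview". Section 12.1 says "only the Data manager and Physicians from UMCU carrying out the interviews will have access to subjects' personal data (Sponsor/Investigator and Julius Clinical". Appendix 2 attributes the data manager to the contract organisation and the physicians to UMCU, so the interviewing physicians are the sponsor/investigator side of that pairing. Section 8.7 leaves it to the investigator whether to approach a lost subject's back-up contact. Section 8.1.2 lists COVID-related hospital, ICU and breathing-support episodes as endpoints fed by the surveys, interviews and app. Section 10.5 compares the 8.1.2 endpoints within each period, with percentages taken over the subjects in each condition.

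**Algorithm versions.** Section 10, on development and validation, says: "Data collected during the Learning Phase will then be used to develop second versions of the algorithms". Section 3.3 agrees, and 3.7 fits with it. Section 10.7 says the algorithms in both conditions "will be updated using data gathered throughout the study and a new version will be implemented in Period 2 of the study".

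**The concern.** There are two separate weaknesses.

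First, knowledge of the sequence is given to whole organisations with no limit by role, although no described task of the interviewers or of those chasing lost subjects needs it. Whether an admission counts as COVID-related, how far an interviewer probes, and whether a back-up contact is called all involve discretion. Someone who knows the condition may exercise it differently between conditions. The items exposed are the healthcare-use endpoints, which serve the first secondary objective, and the completeness of follow-up by condition.

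Second, the primary analysis evaluates the V2 red light in Period 2, so what V2 is must be unambiguous. Two sections build it from one phase and a third section uses wider wording. Section 10 also describes development as continual during the trial. Without one stated data source and a freeze point, a reader of the results cannot tell which data shaped the index test, or confirm that it stayed the same through Period 2.

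**Working it through.** No arithmetic applies. The check is a comparison of passages.

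**Step 1: who needs the sequence and who has it**

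| Function | Where described | Inside a body that 8.2 names as aware? | Does a described task need the sequence? |
|---|---|---|---|
| Back-end selection of the algorithm | 6.1 | Yes; it is part of the manufacturer's product | Yes |
| Interviews on hospital episodes and device effects | 8.4.16, 12.1, Appendix 2 | Yes (sponsor/investigator) | No |
| Decision to pursue lost subjects | 8.7 | Yes (investigator) | No |
| Seriousness of device effects | 9.2.2 | Yes (investigator or delegate) | No |
| Serology and study PCR | 8.4.8, 8.4.12, Appendix 2 | Not named; holds pseudonymised results | No |

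No section masks any role within the three bodies. That a particular interviewer sees the sequence is an inference, because 8.2 names organisations and not roles, but nothing in the protocol prevents it.

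**Step 2: where knowledge of the sequence could change a result**

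- *Primary comparison (10.2).* The index result is an automated red light. The reference is serology at the end of Period 2 or a positive virus test. A physician's diagnosis enters only for subjects not alive at the end of Period 2 who have no test result, and it requires a supportive CT scan. There is little room for judgement.
- *Device effects (10.6).* They are listed without a statistical summary, and every subject wears the same bracelet in both conditions (3.1). There is no between-condition estimate to bias.
- *Healthcare use (8.1.2, 10.5).* The COVID-related label rests partly on interviews and is compared by condition. It is exposed.
- *Retention (8.7).* Follow-up of lost subjects is discretionary and unmasked. It is exposed.

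**Step 3: the data behind V2**

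| Section | Data used for the version run in Period 2 |
|---|---|
| 3.3 | Learning Phase |
| 10, development and validation | Learning Phase |
| 3.7 | Vaccinated subjects should be present in the Learning Phase for V2; consistent with the two above |
| 10.7 | Data from throughout the study; read literally, this includes Period 1 |

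Under 3.3, Learning Phase subjects all receive the experimental algorithm once their baseline is set, so sequence does not yet affect those data. In Period 1 the conditions differ by sequence, so whether Period 1 data may be used is a real question. None of these sections gives a date or event at which V2 is fixed.

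**The case against.** The case on the other side is substantial, and much of it stands.

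*Single-blinding is a declared design.* This is correct: 8.2 contradicts nothing. Some manufacturer access is unavoidable because the back-end is part of its product. The point is only that the knowledge extends further than any described task requires.

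*A reader might infer that everyone but the subject is unmasked.* The protocol does not support that. Three bodies are named, the laboratory is not among them, and virus testing goes first to the municipal service outside the trial. Appendix 2 describes the shared analytics platforms as holding "Pseudonymized data from AVA (bracelet and symptom diary), Surveys, COVID-19 test results, Hospitalization events"; sequence is not on that list.

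*A reader might infer biased judgements of device relatedness or seriousness.* The same bracelet is worn in both conditions and device effects are only listed, so this does not follow.

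*A reader might infer that an unmasked manufacturer could steer the primary result through the V2 threshold, perhaps by the 1.5 to 3 points of specificity in Table 4.* The protocol gives no threshold value or operating curve, so no shift can be derived. Masking the sequence would not prevent tuning either: every subject supplies diary and bracelet data, and both algorithms can be run on the same subject (section 10). Improving V2 before its test in Period 2 is the stated design.

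*Healthcare-use data begin with a blinded subject's self-report and follow a structured interview (8.4.15, 8.4.16).* This narrows the room for bias but leaves the COVID-related label and the depth of probing open.

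*Section 10.7 may be loose wording that also covers the final version, which 3.3 builds from all study data.* That is the likeliest explanation. However, the sentence ties the update to the version implemented in Period 2, so the text still needs correcting. It does not show that Period 1 data will be used.

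*Access rules may sit in documents not shown.* They may, but they would have to narrow a protocol statement that currently grants the knowledge without limit.

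**Conclusion.** The point holds as a modest, inexpensive improvement. Unrestricted knowledge of the sequence is an avoidable source of bias in the interview-based secondary healthcare-use endpoints and in retention. The primary reference standard and the device-effect listings are little affected. The size of the bias cannot be calculated from the protocol.

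The conflict between 3.3 and section 10 on one side and 10.7 on the other is a plain inconsistency. With no freeze point, it leaves the primary index test in Period 2 less well defined than it should be.

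The first part rests on the inference that staff of a body named in 8.2 can learn the sequence. Masking would also be incomplete: under 3.3 and 3.4, a subject who mentions a red light without having had symptoms suggests the experimental condition.

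**What to change.** 1. Amend 8.2 so that the sequence is held only in the app configuration and by one designated unmasked data manager. Healthcare-use and device-effect interviewers, those judging COVID-relatedness and loss to follow-up, and the trial statisticians stay masked until the Period 2 database is locked. Provide a documented unmasking route.
2. Amend 10.7 to match 3.3: V2 is developed from Learning Phase data only and frozen, with version and date recorded, before the first subject enters Period 2. Reserve the use of all study data for the final version, as 3.3 already does.

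The cost is protocol wording, role-based access settings and the unmasking route. By-condition estimates before lock, such as the interim performance estimates in 10.7, would have to come from the unmasked role or wait. Sample size, procedures and subject burden do not change.
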